Each rehabilitation center will recruit around 10 to 20 patients, up to a total of 100 participants. A post hoc sensitivity analysis was performed using G*Power Software Version 3.1.9.7 (Faul et al., 2007) to determine the minimum effect size that could be achieved with 100 participants. A post hoc power analysis for an independent-sample t-test was conducted assuming one-tailed testing. For effect size varying from large (d = 0.8) to small (d = 0.2), 80% power and alpha error probability of α = 0.05 a sample size interval of at least 12 to 156 participants is suggested. With a sample of 100 participants to be included in this study and 80% power the effect size is estimated at 0.25. Each participant must have a npABI and be between the ages of 21 and 65, in order to avoid confusing the issues of ageing and non-progressive acquired brain injury, people over 65 were excluded from the study and treated at their center for routine care. All participants must have held a Category B driving license (light vehicles) for at least 3 years and have driven a minimum of 10,000 km, so as not to assess novice drivers. They have been examined by the PRM doctor, who confirms that there are no contraindications to driving other than the pathology under study. They also gave their consent to take part in the PREVAC study. The ethical committee has classified this research as a non-interventional, involving no risk or constraint for participants, and in which all procedures are carried out in the usual way. They must not have a medical condition (other than npABI) that is incompatible with maintaining their driving license, according to the list of conditions mentioned in the decree of March 28, 2022. They must not have any oral comprehension disorders that can be perceived by the therapist, must not be pregnant (to avoid an interruption of pregnancy in the event of an accident and the resulting psycho-social and legal risks), and must not be under the influence of any Level 3 medication that could present a driving risk.

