##### Main criterion: concordance between professional assessments

2.3.1.1

To meet the main objective, the concordance of the results of the neuropsychological assessment, RDA and multiprofessional evaluation will be studied in pairs (agreement between professional assessments). Each professional involved in the study will give a “favorable,” “reserved” or “unfavorable” opinion based on their practice. Evaluation criteria will correspond to cross-tabulated numerical values of results from each assessment tool studied (neuropsychological assessment, RDA and multiprofessional evaluation). “Reserved” opinions indicating driving restrictions will initially be classified as “unfavorable,” so that the results can be expressed as a binary Favorable/Unfavorable variable for each assessment. The RDA results will also include the number of driving instructor interventions on pedals, steering wheel and other car controls, using categorical variables. The values *a*, *b*, *c* and *d* (Table 1) will be used to perform the concordance test detailed in the next section (“Statistical analysis”).

**Table 1 tab1:** Evaluation criterion of the main objective for contingency table.

		Assessment x_i_	
		Favorable	Unfavorable
Assessment x_ii_	Favorable	*a*	*b*
	Unfavorable	*c*	*d*

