#### Statistical analysis

2.3.3

To meet the main and secondary A and B objectives, concordance tests will be used to verify that two independent abilities to resume driving measures (two tests) of the same modality—“Favorable” or “Unfavorable”—are equal. Concordance analyses between tests (binary variables) will be expressed in the form of concordance percentages, simple kappa coefficient and its 95% confidence interval. Analyses between TRIP (continuous variable) and other tests (binary variables) will be conducted using *t*-tests or Mann–Whitney tests depending on the TRIP score distribution. Multivariate regression will also be used to study measures’ concordance and prediction levels, for both objectives. It will be logistic or linear, depending on the studied variable (i.e., approved doctor’s opinion for objective A and TRIP results for objective B).

A sensitivity and specificity analysis of the approved doctor’s opinion will also be carried out. Performance metrics (Secondary Objective C) will be calculated from the confusion matrix values (Table 4):$$\mathrm{Accuracy:}\frac{RP+RN}{RP+RN+FP+FN}$$$$\mathrm{Sensitivity (Se):}\frac{RP}{RP+FN\text{.}}$$$$\mathrm{Specificity (Sp):}\frac{RN}{FP+RN}$$$$\mathrm{Positive predictive value (PPV) or Precision (Pr):}\frac{RP}{RP+FP}$$$$\mathrm{Negative predictive value (NPV):}\frac{RN}{FN+RN}$$

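### The stated effect size (0.25 at 80% power) belongs to a t-test and does not describe the main criterion, a kappa between binary opinions; it is also wrong for the one t-test planned

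*Protocol article*

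**What the plan says.** Section 2.1 fixes the sample by recruitment: "Each rehabilitation center will recruit around 10 to 20 patients, up to a total of 100 participants". It then reports what that number can detect. The method is stated as "A post hoc power analysis for an independent-sample t-test was conducted assuming one-tailed testing". For d from 0.8 down to 0.2, the text reads "80% power and alpha error probability of α = 0.05 a sample size interval of at least 12 to 156 participants is suggested", and it closes with "With a sample of 100 participants to be included in this study and 80% power the effect size is estimated at 0.25". No other place in the article sizes the study.

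The main criterion is in 2.3.1.1: "the concordance of the results of the neuropsychological assessment, RDA and multiprofessional evaluation will be studied in pairs". Reserved opinions are first counted as unfavorable, so each opinion is binary and each pair forms a 2x2 table. Section 2.3.3 gives the statistic: "Concordance analyses between tests (binary variables) will be expressed in the form of concordance percentages, simple kappa coefficient and its 95% confidence interval".

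The same section plans a t-test, or a Mann-Whitney test, for the continuous TRIP score against the binary opinions. Section 2.3.1.2 lists the comparison with TRIP as secondary criterion B. Section 2.1 calls the study exploratory, and 2.4 makes no assumption about how far the opinions will agree.

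**The concern.** A standardized mean difference needs a continuous outcome and, for the test named, two independent groups. The main criterion has neither: the outcome is binary and every participant receives every opinion. A d of 0.25 therefore cannot be turned into a power or a precision for kappa or percent agreement.

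A reader of 2.1 sees 80% power for a small effect and is not told that this leaves the main criterion unaddressed. Sections 3.1.1 and 3.1.2 then draw conclusions about the neuropsychological and on-road assessments according to whether the opinions are concordant or discrepant. How firmly 100 participants can support either reading depends on the width of the kappa interval, and 2.1 gives no indication of it.

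**Working it through.** **1. Reproducing the stated t-test figures.** Inputs from 2.1: one-tailed, alpha 0.05, power 80%, d = 0.8 and 0.2, and 100 participants. Results are from the noncentral t distribution.

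| Quantity | Article | Independent-sample t-test | One-sample or paired t-test |
|---|---|---|---|
| N for d = 0.8 | 12 | 42 (21 per group) | 11.1, so 12 |
| N for d = 0.2 | 156 | 620 (310 per group) | 155.9, so 156 |
| Detectable d at N = 100 | 0.25 | 0.50 (50/50 split) | 0.250 |

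All three printed figures match a one-tailed one-sample or paired test. None matches the independent-sample test that the text names.

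**2. The t-test actually planned (TRIP score by opinion).** This is an independent-groups comparison. The normal approximation shows the source of the gap: detectable d = (1.645 + 0.842) / sqrt(n1 n2 / (n1 + n2)).

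- 50/50: 2.487 / sqrt(25) = 0.497; noncentral t gives 0.50.
- 70/30: 2.487 / sqrt(21) = 0.543; noncentral t gives 0.55.
- One sample of 100: 2.487 / sqrt(100) = 0.249; noncentral t gives 0.250, the article's figure.

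Power at d = 0.25 is 34% at 50/50 and 31% at 70/30. Even 100 per group, which is twice the planned total, would give a detectable d of 0.35. The splits are assumptions, because the article gives no expected share of favorable opinions.

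**3. What 100 participants give for the main criterion.** The article states no expected kappa, agreement or favorable rate, so ranges are assumed. With equal margins p (the share favorable) and all n participants analysed, the large-sample variance of kappa (k) in a 2x2 table is

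Var(k) = (1/n)(1 − k)[(1 − k)(1 − 2k) + k(2 − k) / (2p(1 − p))], and the half-width is 1.96 × sqrt(Var).

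Example, k = 0.6, p = 0.5, n = 100: 0.4 × [0.4 × (−0.2) + 0.84 / 0.5] = 0.4 × 1.60 = 0.64. The SE is sqrt(0.64 / 100) = 0.080 and the half-width is 0.157.

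Example, k = 0.6, p = 0.8: 0.4 × [−0.08 + 0.84 / 0.32] = 0.4 × 2.545 = 1.018. The SE is 0.101 and the half-width is 0.198.

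| Favorable | kappa 0.4 | kappa 0.6 | kappa 0.8 |
|---|---|---|---|
| 50% | 0.180 | 0.157 | 0.118 |
| 70% | 0.195 | 0.172 | 0.129 |
| 80% | 0.221 | 0.198 | 0.149 |

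For percent agreement the half-width is 1.96 × sqrt(A(1 − A) / 100): 9.0 points at 70%, 7.8 at 80% and 5.9 at 90%.

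**The case against.** The strongest reply is that 2.1 never says its figure serves the main objective. It describes a sample fixed by recruitment and reports a generic minimum effect. The study is exploratory and has no concordance hypothesis, so no power calculation for kappa was owed. A t-test is in the plan, 2.3.3 commits to a 95% CI for each kappa so imprecision will be visible in the results, and an expected width could be left to the full protocol.

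Much of this stands. The article makes no explicit power claim for the main objective, and the planned kappa analysis is sound. The exploratory aim also argues for a precision statement rather than a power figure. What does not stand is the sizing statement as printed. It is offered without limitation as what 100 participants can achieve, it does not apply to the main criterion, and it is numerically wrong for the one planned analysis it could apply to. That is a fault in printed text, not a detail left to another document.

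Stronger readings are tempting and should be resisted:

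- A reader might infer that the study is underpowered for kappa. That requires choosing a null and an alternative kappa, and 2.4 makes no assumption about concordance. Any such power would rest on a contrast the documents do not contain, and setting it against the printed 80% would compare unlike quantities.
- A reader might extend the consequence to 3.1.3. That section concerns agreement between the multiprofessional opinion and the approved doctor, which is secondary criterion A.
- A reader might look only at the widest intervals. The multiprofessional opinion is formed from the other assessments (2.2.1.5), so high agreement is plausible in two of the three main pairs, and the kappa 0.8 column is as relevant as the others.

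**Conclusion.** The point holds as a fault in the sizing statement. The printed effect size and power do not describe the main objective, and 0.25 does not hold for the TRIP comparison either, where the detectable d is about 0.50 or larger.

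For kappa between 0.4 and 0.8 and 50% to 80% favorable, 100 participants give a 95% CI half-width of about 0.12 to 0.22. As an example, an observed kappa of 0.6 at 80% favorable would run from about 0.40 to 0.80. These widths rest on assumed kappas and favorable rates, equal margins, the large-sample SE and all 100 participants analysed. Section 2.3 does not replace missing data, so fewer analysed participants would widen them.

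Nothing here shows that 100 is too few or that the kappa analysis should change. The documents set no target precision against which the number could fail.

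**What to change.** In 2.1, keep 100 participants and replace the power paragraph with a precision statement for the main criterion. For example: with 100 participants analysed and equal margins, the expected 95% CI half-width for kappa of 0.4, 0.6 and 0.8 is about 0.18, 0.16 and 0.12 if 50% of opinions are favorable, and 0.22, 0.20 and 0.15 if 80% are; for agreement of 70% to 90% it is about 6 to 9 percentage points. Say that these inputs are assumptions.

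Delete the 0.25 figure and the range of 12 to 156. If a t-test figure is wanted, give the independent-sample value (one-tailed, 80% power, d of about 0.50 at 50/50 and 0.55 at 70/30) and label it as applying only to TRIP score by opinion. Relabelling 0.25 without recomputing it would attach a wrong number to a named analysis.

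The cost is one reworded paragraph. No participants are added and no analysis changes, but the stated figures become less favorable.

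### The printed sample sizes (12 to 156) and detectable effect (0.25) are those of a one-sample or paired t-test, not the independent-sample t-test that the article names; the detectable effect is understated at least two-fold

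*Protocol article*

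**What the plan says.** The calculation stands in section 2.1 (Study design and participants). Recruitment comes first: "Each rehabilitation center will recruit around 10 to 20 patients, up to a total of 100 participants". The test is then named: "A post hoc power analysis for an independent-sample t-test was conducted assuming one-tailed testing". Its settings are "For effect size varying from large (d = 0.8) to small (d = 0.2), 80% power" and "alpha error probability of α = 0.05", from which "a sample size interval of at least 12 to 156 participants is suggested". The result for the planned size is: "With a sample of 100 participants to be included in this study and 80% power the effect size is estimated at 0.25".

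Section 2.3.3 (Statistical analysis) plans one use of a t-test. The continuous TRIP score is compared between the two levels of each binary opinion, by t-test or Mann–Whitney test according to the score's distribution. The main criterion (sections 2.3.1.1 and 2.3.3) is pairwise concordance, reported as percentage agreement and a "simple kappa coefficient and its 95% confidence interval".

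**The concern.** Twelve participants in total means six per group, which is far too few for an independent-groups comparison to reach 80% power at d = 0.8. Likewise, two groups of 50 cannot detect a quarter of a standard deviation with 80% power. The figures are in running text and agree with one another, so a broken table or a slip in one number does not explain them.

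What is at stake is what the article tells readers about the TRIP comparison. It credits 100 participants with about twice the sensitivity that the named test has. Section 3.1.2 intends to judge the usefulness of the TRIP grid by its agreement with the other assessments, so readers need a correct idea of how large a TRIP difference this sample can detect.

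**Working it through.** **Inputs (section 2.1).** Independent-sample t-test, one-tailed, alpha 0.05, power 80%, d from 0.8 to 0.2, 100 participants in total. The favorable/unfavorable split is not stated. I take 50/50 as the best case and show 70/30 and 80/20 as assumptions.

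**Method.** Power = P(T > t_crit), where T is noncentral t with df degrees of freedom and noncentrality ncp.
- One-sample or paired: df = n − 1, ncp = d·√n.
- Two independent groups: df = n1 + n2 − 2, ncp = d·√(n1·n2/(n1 + n2)).

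**Step 1: which test gives the printed figures?** One-sample or paired, one-tailed:
- d = 0.8: n = 11 gives power 0.795. n = 12 gives ncp = 0.8·√12 = 2.77 and power 0.829. Required n = **12**, as printed.
- d = 0.2: n = 155 gives 0.798. n = 156 gives ncp = 0.2·√156 = 2.50 and power 0.800. Required n = **156**, as printed.
- n = 100: 80% power is reached at d = 0.2504, which rounds to **0.25**, as printed.

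**Step 2: the named test.** Two independent equal groups, one-tailed:
- d = 0.8: 20 per group gives 0.799, 21 per group gives 0.817. Total 2 × 21 = **42**.
- d = 0.2: 309 per group gives 0.799, 310 per group gives 0.800. Total 2 × 310 = **620**.
- 50 + 50: √(50·50/100) = 5. At d = 0.25, ncp = 1.25 against a critical value of 1.66, so power is **34%**. Power of 80% needs d = **0.501**.
- Ratio of detectable effects: 0.501/0.250 = 2.0.

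**Step 3: other readings.**
- The printed sizes as per-group numbers: the named test needs 21 and 310 per group, not 12 and 156.
- Two-sided independent test: totals of 52 and 788, further away.
- 100 per group instead of 100 in total: detectable d = 0.35, still not 0.25.
- One-tailed correlation test: about 0.247 at n = 100 and about 153 for r = 0.2, but about 8 for r = 0.8, so it does not explain the 12.

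Of the readings tried, only the one-sample or paired test gives all three figures.

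**Step 4: effect of the split.** Detectable d with 100 participants at 80% power:

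| Assumed split | One-tailed | Two-sided |
|---|---|---|
| 50/50 | 0.50 | 0.57 |
| 70/30 | 0.55 | 0.62 |
| 80/20 | 0.63 | 0.71 |

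At 80/20 the one-tailed understatement is 0.63/0.25 = 2.5-fold.

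**The case against.** Several points on the other side are fair.

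- **The sample size does not come out of this calculation.** Section 2.1 fixes up to 100 participants from recruitment and then asks what effect that number can detect. The study is described as exploratory, and section 2.4 makes no assumption about concordance. A reader might infer that the justification for 100 collapses, or that more participants are needed. The article does not support that: 100 is an input, and the kappa analysis does not use these figures. This limits the consequence but leaves the printed numbers wrong.
- **The label might be wrong instead of the numbers.** Section 2.3.2.2 plans within-person differences from before injury to 6 and 12 months, where a paired calculation would be natural. However, the article names no paired t-test for them, and the one t-test it plans is between groups. Which option was selected in the software can only be inferred from the three-figure match. That label and figures disagree does not depend on that inference.
- **Misreading of a null result.** One might predict that a non-significant TRIP comparison would be taken to exclude effects above 0.25. No passage says so; section 3.1.2 says only that discrepancies would lead to the grid's usefulness being discussed. It would also be too strong to say that the named test easily misses d = 0.5: one-tailed power there is about 80% at 50/50 and 74% at 70/30.
- **Sidedness.** Section 2.1 has "assuming one-tailed testing", while section 2.3 sets a 5% threshold with 95% confidence intervals and does not say whether tests are one- or two-sided. That is unclear, but it is not a demonstrated contradiction.
- **Precision of kappa.** An article may leave this to the full protocol, so its absence is not counted as a fault here.

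**Conclusion.** The point holds as a mismatch between the named test and its printed results. For the one-tailed independent-sample t-test the totals are 42 and 620, not 12 and 156. The detectable effect with 100 participants is 0.50 at best, not 0.25, and power at 0.25 is 34%, not 80%. The understatement is two-fold at an equal split and grows with imbalance. The totals and the 0.50 rest only on inputs stated in section 2.1 plus equal groups; the figures for unequal groups rest on assumed splits. This is an error in a stated calculation about a secondary comparison. It does not show that the design fails or that the main concordance analysis is undersized.

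**What to change.** In section 2.1:

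1. Replace 12, 156 and 0.25 with the figures for the named test: 42 and 620 in total, and a detectable d with 100 participants of about 0.50 one-tailed (0.57 two-sided) at 50/50, 0.55 (0.62) at 70/30 and 0.63 (0.71) at 80/20. Label the split as an assumption.
2. State the sidedness that the TRIP comparison will actually use, and quote the matching figures.
3. Say that this calculation concerns the TRIP comparison and not the main kappa criterion.
4. Optionally, add the expected precision of kappa at n = 100: a 95% confidence interval half-width of about 0.12 to 0.22 for kappa between 0.4 and 0.8 with 50% to 80% favorable opinions (large-sample standard error, equal margins). The article gives none of these inputs, so they must be marked as assumptions.

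If a paired comparison was what the authors meant, they should instead name it and say which planned analysis it serves. Either way the change is to text only. No extra participants are needed; the cost is a less favorable stated figure.

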### Study protocol

2.2

#### Cross-sectional study

2.2.1

Each participant’s driving ability is assessed by experienced field assessors as follows:

##### Consultation with a PRM doctor

2.2.1.1

The purpose of this medical consultation is to check the inclusion/non-inclusion criteria and define the pathology(ies) and list the medication prescribed and taken by the participant, in order to study their possible influence on driving ability. These sensitive data are not investigated in the study but may be partially mentioned in the final multiprofessional opinion.

##### Neuropsychological assessment

2.2.1.2

This assessment is carried out by a psychologist specialized in neuropsychology. It includes a series of validated standardized tests investigating attentional, executive and psycho-behavioral functions. The list of tests was co-constructed according to different criteria:- psychometric qualities (sensitivity, validity, reliability)- relevance established in the literature in relation to driving ability evaluation- availability and frequency of use in current practice (assessed through a survey of rehabilitation centers)- administration conditions (essentially non-verbal tests for use with patients with expressive aphasia; non-bimanual tests allowing inclusion of patients with hemicorporeal deficits; duration deemed acceptable and equipment easy to obtain and use).

The neuropsychological assessment lasts around 3 h, divided into two one-and-a-half-hour sessions, each with a five- to ten-minute break. The order of administration of the tests was established so as to alternate tasks according to their format (computerized vs. paper-and-pencil), their mental load (higher or lower), their sensitivity to fatigue, and the cognitive functions called upon. The standardized neuropsychological assessment protocol is described in the case report form. It includes the following tests: Alertness (TAP 2.3.1), Divided attention (TAP 2.3.1), Epworth scale, Trail-Making-Test (TMT), Go/Nogo (TAP 2.3.1), Basic Empathy Scale in Adults (BES-A), Neglect with central task (TAP 2.3.1), Tour of London (TOLDX 2^nd^ edition), Working memory difficulty level 3 (TAP 2.3.1), Sustained attention color-or-form version (TAP 2.3.1) and UPPS Impulsive Behavior Scale. Lastly, the Brain Injury Driving Self-Awareness Measure—BIDSAM (Gooden et al., 2017) is part of the neuropsychological assessment, but will be completed following the RDA.

For each test, the examiner collects raw and standardized scores (each participant’s performance is compared to the standard group). Based on this assessment, the neuropsychologist then issues an opinion (favorable, unfavorable or reserved) on the estimated compatibility between the participant’s cognitive functions and the return to driving.

##### Occupational therapy assessment

2.2.1.3

The occupational therapist carries out this assessment according to a non-standardized protocol, in order to investigate the participant’s sensory-motor functions, and to consider possible vehicle adaptations. His role is mainly to determine the necessary adaptation of the participant’s car and, thanks to the pluriprofessional advice given at the end of the process, to pass on his opinion to the approved doctor. The occupational therapist also administers questionnaires to obtain information on the participant’s driving before brain injury: Driving Habits Questionnaire (DHQ), Driving Behavior Questionnaire (DBQ) and perceived road risk.

